### Sample size

Sample size calculations are based on a between-group comparison of post-treatment scores at 12-weeks follow-up post-randomisation on our primary outcome measure (WSAS), assuming a significance level of 0.05 with a standard deviation of 8.5 for that measure; this standard deviation was taken from Proudfoot *et al*.
[6], whose study used the same intervention, outcome measure and follow-up interval.

A sample size of 35 per group (total 140 patients) is sufficient to detect main effects (brief vs. extended, and clinician vs. assistant) of 0.477 standard deviations (about 4.1 points) in our primary outcome measure with 80% power, or of 0.522 (about 4.4 points) in our primary outcome measures with 90% power. The estimated sample size of 140 patients with available data can detect an interaction effect (for example, the difference between brief and enhanced, compared between clinician and assistant) of about 0.961 standard deviations (about 8.2 points) on our primary outcome measure with 80% power.

Allowing for a 30% drop-out rate, we intend to randomise 50 patients in each of the four groups (total 200 randomised patients). We estimate that about a third of all screened patients may be unsuitable for the trial or refuse participation (based on a similar pragmatic trial by Marks *et al*.
[48]), therefore to achieve 200 randomised patients we aim to recruit a total of 300 referrals.

Our sample size calculation and effect estimates are conservative. Our hope is that adjustment by the corresponding baseline outcome measure reduces the standard error of the effect estimates and hence increases the power for a given sample size.

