### Statistical analysis

Descriptive statistics will summarise demographic and clinical features of those referred, those randomised, those who complete the intervention (at least 5 cCBT sessions) and those who complete at least one set of post-baseline outcome measures. The same variables and baseline values of the outcome measures will be compared between brief and extended support, and between clinician and assistant at baseline. Where large differences exist, these variables will be included as potential confounders. Our primary analysis will be based on the first batch of completed postal questionnaires returned by the patients. These are posted out to the patients at 12 weeks post-randomisation but the timing of receiving completed questionnaires from the patients is variable. The time of receipt is recorded and may be included as a covariate.

Linear models will be used to estimate the main effects of the two treatments. An estimate and confidence interval for the interaction term will be obtained. Corresponding adjusted estimates will be obtained adjusting for baseline only, and for baseline and the potential confounders identified at baseline. Effect sizes will be calculated using Cohen’s d
[49]. The number of patients showing clinically significant and reliable change
[50] will be reported where possible. C-PAS and T-PAS will be compared for each group using mixed-effects models and their similarity will be assessed using intra-class correlation.

The primary analysis will include patients in the groups to which they had been randomly assigned regardless of the actual treatment they have received. The primary analysis will include non-missing data only, but the baseline characteristics of missing and non-missing values will be compared to assess the pattern of missing data. Further, as recommended by Altman
[51], sensitivity analyses will be performed by employing multiple imputation techniques. Where a few items within a scale are missing for an individual participant we will impute using that person’s scale average.

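### Three versions of each main effect on 12-week WSAS are planned and none is named as the basis of the conclusion; the baseline-adjusted model should be

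*Protocol article*

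**What the plan says.** The Sample size section sizes the trial "based on a between-group comparison of post-treatment scores at 12-weeks follow-up post-randomisation", "assuming a significance level of 0.05 with a standard deviation of 8.5 for that measure". No baseline adjustment enters the calculation. The section calls the result conservative and adds: "Our hope is that adjustment by the corresponding baseline outcome measure reduces the standard error of the effect estimates".

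The Statistical analysis section plans linear models for the main effects of the two factors, with an estimate and interval for the interaction. It continues: "Corresponding adjusted estimates will be obtained adjusting for baseline only, and for baseline and the potential confounders identified at baseline". The potential confounders are variables that turn out to differ greatly between the compared groups at baseline; no threshold for a large difference is given. Time of questionnaire receipt is a further covariate that may or may not be included.

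The section uses the term primary analysis for three things: the first batch of returned postal questionnaires, analysis in the groups as randomised, and use of non-missing data. It never attaches the term to one of the models.

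**The concern.** Brief versus extended support and clinician versus assistant support are two questions, and each will get three answers. Two things could go wrong, and they belong to different readings of the text.

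- If the choice is open, it can be made after the results are seen. The third model adds to this, because its covariates depend on the observed data.
- If the unadjusted estimate becomes the headline by default, the conclusion rests on what may be the least precise of the three, although baseline WSAS has been collected and the protocol itself expects a gain from using it.

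These are alternatives and do not add up: a settled headline leaves no choice to abuse, and an open choice does not necessarily lose precision. One sentence naming the primary model removes both.

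**Working it through.** **Inputs from the Sample size section.** SD 8.5 points; alpha 0.05 (taken as two-sided, which reproduces the stated figure); 35 per cell, so 70 versus 70 for each main effect; detectable effect "of 0.477 standard deviations (about 4.1 points) in our primary outcome measure with 80% power".

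**Input not in the protocol.** The correlation r between baseline and 12-week WSAS. A range of 0.3 to 0.7 is assumed, with r = 0 as reference.

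**Step 1: reproduce the plan's figure.** The SE of an unadjusted main effect is 8.5 × √(2/70) = 1.44 points. By the noncentral t distribution with 138 df, power at 0.477 SD is 80.0% (80.6% by the normal approximation). In points, 0.477 × 8.5 = 4.05, which the protocol rounds to 4.1. The 80% figure is therefore the power of the unadjusted comparison.

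**Step 2: add baseline WSAS.** The residual SD becomes 8.5 × √(1 − r²), and the SE shrinks by the same factor. Residual df are 140 − 4 = 136.

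| r | √(1 − r²) | SE, points | Detectable at 80% power, points | Power at 0.477 SD |
|---|---|---|---|---|
| 0 | 1.000 | 1.44 | 4.05 | 80.0% |
| 0.3 | 0.954 | 1.37 | 3.87 | 83.6% |
| 0.5 | 0.866 | 1.24 | 3.51 | 89.9% |
| 0.7 | 0.714 | 1.03 | 2.90 | 97.5% |

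Example at r = 0.5: 0.477 × 0.866 × 8.5 = 3.51 points.

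**Step 3: the cost of adjusting.** The two-factor model without baseline has 137 residual df, and with baseline 136. Adjustment breaks even at about r = √(1/137) = 0.09. Baseline questionnaires are returned before randomisation (Treatment allocation section), so adjustment should lose few or no patients.

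**Step 4: the cost of an open choice.** A simulation under no effect used 10,000 runs per value of r, 140 patients, baseline correlated r with the outcome, and one further covariate with coefficient 0.2 on the standardised outcome. All three models were fitted to each data set. Each model alone rejected in about 5% of runs. Reporting an effect whenever any of the three was significant rejected in 7.3% (r = 0.3), 8.2% (r = 0.5) and 9.3% (r = 0.7) of runs, per main effect.

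**Side check on the 90% claim.** The section also states power for an effect "or of 0.522 (about 4.4 points) in our primary outcome measures with 90% power". The unadjusted comparison gives 86.6% at 0.522 SD; 90% needs 0.552 SD, or 4.7 points. That mismatch is a separate matter, but baseline adjustment would bring 0.522 SD to 90% once r is about 0.32.

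**The case against.** The strongest reply has four parts.

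1. **Baseline adjustment is already planned.** The baseline-adjusted estimate is promised, and the sample size text expects it to help. This stands: only the rank of the model is unstated, not its presence.

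2. **An unadjusted analysis is legitimate.** Under randomisation it is unbiased, it matches the basis of the sample size, and its interval already allows for chance baseline imbalance. This stands, and for that reason the point is about efficiency and discretion, not validity.

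3. **Ranking models belongs in the analysis plan.** The document is a condensed article, and a separate plan may name the primary model. This is a fair limit. But the article does set out its model strategy, and it sets out three answers side by side without ranking them, one with covariates chosen from the data. The recommendation also goes beyond recording a missing detail, because it puts a more efficient model, fixed in advance, under the conclusion.

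4. **The gain rests on an undocumented correlation.** This stands. At r = 0.3 the detectable difference moves only from 4.05 to 3.87 points.

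A reader might infer that the unadjusted comparison is the designated lead analysis, from the order of the sentences, the word *corresponding* and the basis of the sample size. The protocol never says so. Nor does it propose to report whichever model is significant; the 7.3% to 9.3% shows what an open choice would permit, not what is planned.

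**Conclusion.** The point holds as one of designation. Three versions of each main effect are planned, none is named as the basis of the conclusion, and the third has covariates that depend on observed imbalance. No systematic bias follows, because each model is valid alone if fixed in advance.

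Naming the baseline-adjusted model would cut the SE of a main effect by about 5% at r = 0.3, 13% at r = 0.5 and 29% at r = 0.7. These figures assume 140 analysed patients, SD 8.5, two-sided alpha 0.05 and a linear relation with baseline. To call adjustment more precise without condition, or free of any cost, would claim more than the document supports: r is not given, one degree of freedom is spent, and below about r = 0.09 nothing is gained. The change is nonetheless worth making, since the possible gain is large and the cost very small.

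**What to change.** Add to the Statistical analysis section: *The primary analysis of each main effect is a linear model of 12-week WSAS on the two randomised factors and baseline WSAS. The conclusion rests on this model. The unadjusted model, and the model further adjusted for variables showing baseline imbalance, are sensitivity analyses.*

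Apply the same rule to each secondary outcome that has its own baseline value, such as BDI, BAI and EQ-5D. Keep covariates chosen from observed imbalance, and time of receipt, out of the primary model.

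The cost is one sentence, to be fixed before outcomes are compared by group, and one degree of freedom. It needs no new data and no extra patients, and all three models are still reported. The sample size can stay as it is.

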The study also aims to evaluate the process of recruiting and screening patients with depression for cCBT, to explore effect modifiers (specifically severe vs. mild/moderate depression or anxiety, and referrals from general practitioners (GPs) vs. mental health professionals) and predictors of cCBT usage and outcomes, to indicate the most appropriate measures for assessing clinical outcomes with cCBT, and to compare the computer and the support person with respect to creating and maintaining a therapeutic alliance with the patient. To this end, the study has the following secondary objectives:

1. To compare the characteristics of referrals for cCBT who take up the offer for assessment and treatment with the characteristics of referrals who drop out before randomisation (refusals).

2. To assess whether a clinician or an assistant can reliably predict patient suitability for cCBT by reviewing patients’ written responses to a standardised questionnaire.

3. To explore whether outcomes and satisfaction with different levels of support for cCBT vary for certain sub-groups of patients (severe vs. mild/moderate depression or anxiety and referrals from GPs vs. mental health professionals).

4. To investigate whether patient characteristics and treatment group predicts clinical outcomes, number of cCBT sessions completed, and patient satisfaction.

5. To assess the similarity of various standardised self-report questionnaires for the assessment of depression, anxiety and functioning and quality of life.

6. To compare and assess the similarity of alliance ratings and explore patients’ experiences using a computerised self-help system vs. speaking to a support person on the telephone.

7. To identify common themes and key differences in the content and style of brief vs. extended support and of clinician vs. assistant support.

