### cCBT

The computerised cCBT system used in this study is Beating the Blues (BtB) marketed by Ultrasis Ltd based in London, UK. This was chosen because at the time of the study set-up it was the cCBT system recommended in the UK by the National Institute for Clinical Excellence (NICE)
[3] and the Department of Health (DH)
[32] as an effective and cost-effective treatment method for mild-moderate depression in primary care. During eight 50-minute sessions, BtB uses text, videos, voice instructions, diagrams and pictures to teach patients how to identify unhelpful thoughts and come up with helpful alternatives, and how to perform activity scheduling, problem-solving and other relevant homework tasks between their computer sessions. Each computer session builds on the one before and its completion triggers printing of a progress report.

Most patients use the computerised therapy system from home; those who do not have access to a computer, or who wish to use the system outside their home environment, can access the cCBT system in public places such as libraries, community centres or Internet cafes and are reimbursed for their expenses. Patients go through BtB at their own pace, but it is suggested that they cover a module per week, allowing enough time in-between sessions for homework (for example, rehearsing practical tasks or keeping diaries), with the aim of completing the whole programme within 12 weeks.

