### Data collection

Baseline demographic and clinical characteristics are obtained by the self-referral questionnaire which is completed by patients and posted to the research team before randomization. The self-referral questionnaire has been suitably adapted for the purpose of this study from its previous validated version
[33]. The questionnaire has nine sections which elicit quantitative and narrative data about patients’ symptoms, computer literacy, lifestyle, past and present treatments including medication, and therapy goals and preferences for therapist-delivered interventions vs. computerised self-help.

Data on clinical outcomes, resource use and patient experiences are collected in two ways: both by post and electronically. Postal questionnaires are sent to patients at baseline (randomization) and then at weeks 12 (primary end-point) and 24 (follow-up) post-randomization with instructions to complete them and return to the research team. Electronic data are collected automatically by the cCBT system during each cCBT session. The timing of electronic data collection is recorded by the cCBT system but it varies according to the frequency with which patients log into it.

Narrative data are also collected during a 15 to 30 minute assessment with the patient pre-randomization, as part of support sessions by the clinician and the assistant, and during a 15 minute telephone interview, which asks about patient views and experiences of using a computerised self-help system and of having telephone support at 12-weeks post-randomization, by the study’s research associate (JM).

Below we give a detailed description of individual data collection tools and justification for their inclusion in the study. All standardised measures are self-reported and are collected independently of the staff proving telephone support; there are no observer-rated outcomes so there is no need for blinding.

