A per-protocol analysis will also be performed on the main outcomes using completers only, which we define as those patients who complete at least 5 cCBT sessions. We will compare sub-group effects by including interaction terms in appropriate linear models. We will use linear models to investigate which demographic and clinical variables predict primary outcome, session completion and patient satisfaction. Interaction terms may be included to investigate which variables modify the main effects. Secondary analysis will be carried out using the electronic data collected by the cCBT system in every session. The series of session electronic outcomes will be summarised and compared between treatment groups using repeated measures analysis.

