### Ethical issues

Approvals were granted by a regional NHS Research Ethics Committee and the Research & Development (R&D) departments of the relevant NHS Trusts. Patient consent is obtained by post. Patients are advised to return the consent form and self-referral questionnaire by post and not by email, to protect confidentiality. Patients can withdraw from the study at any point, without providing a reason, but data collected up to their withdrawal will still be used. Patients retain cCBT access for 24 weeks even if they choose not to speak to the support staff. If a patient needs further treatment upon completion of the study, research staff can directly make a referral to the local psychological therapies service or discuss treatment options with the patient’s GP.

Patients’ research data are stored on a password-protected laptop. Information recorded on the cCBT system can only be accessed by the Chief Investigator, the study’s research administrator and the individual member of staff who offers support to each patient. The support staff do not have access to any named individual feedback about experiences of therapy. Anonymised electronic data (such as demographic information, clinical outcome ratings, extracts from patient interviews and therapist field notes) are accessible only by research and clinical staff involved in the study. Digital recordings are wiped once the transcribed data are stored safely and all identifying information is omitted from transcripts. Archive copies of postal questionnaires and transcripts will be retained for 10 years and then disposed of in accordance with the University and NHS guidelines.

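### The per-protocol completer rule (five or more cCBT sessions) is not tied to the date of the outcome, so sessions done after the week-12 WSAS can decide who enters the analysis of that score

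*Protocol article*

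**What the plan says.** The Statistical analysis section of the protocol article states that a per-protocol analysis will be "performed on the main outcomes using completers only, which we define as those patients who complete at least 5 cCBT sessions". Earlier in the same section the descriptive summaries use the same threshold, for "those who complete the intervention (at least 5 cCBT sessions"). Neither place gives a date, a week or a link to return of a questionnaire.

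The timing of outcomes and of treatment is set out elsewhere in the article:

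- **Outcome.** Data collection places the postal questionnaires "at weeks 12 (primary end-point) and 24 (follow-up) post-randomization". Statistical analysis adds that the first batch is "posted out to the patients at 12 weeks post-randomisation but the timing of receiving completed questionnaires from the patients is variable", and that the time of receipt is recorded.
- **Pace.** The cCBT section says "Patients go through BtB at their own pace". One module a week is a suggestion, and finishing all eight sessions in 12 weeks is an aim.
- **Support.** The Telephone support section offers up to 12 calls spread over 12 to 24 weeks, depending on the patient's speed.
- **Access.** Ethical issues states: "Patients retain cCBT access for 24 weeks even if they choose not to speak to the support staff".
- **Session dates.** Data collection states: "The timing of electronic data collection is recorded by the cCBT system".

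**The concern.** A per-protocol analysis of the week-12 WSAS is meant to describe the support contrasts in patients who had received an adequate amount of the programme. Sessions done after the score was given cannot have contributed to it. If the completer flag is set from the total number of sessions over the whole access period, a patient with three or four sessions at week 12 who later reaches five is analysed as someone who had completed treatment when the WSAS was measured. The week-12 set then depends in part on what patients did after the outcome, possibly in response to how they were feeling at that time.

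This could matter for the comparison because support type may affect how far patients go. Secondary objective 4 in the Background asks whether "treatment group predicts clinical outcomes, number of cCBT sessions completed". If support affects session use, slow finishers need not be evenly spread between the arms.

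**Working it through.** No figure in the article depends on this rule, so there is no stated number to reproduce. The check has two parts: whether any text limits the session count, and which patients the undated rule would affect.

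**Text.** Statistical analysis, cCBT, Telephone support, Data collection and Ethical issues were read together. None restricts the count to sessions before the questionnaire. The 12-week figure in the cCBT section is an aim for finishing eight sessions and is not part of the completer rule. The 24-week access period and support over 12 to 24 weeks show that later sessions are allowed.

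**Which patients are affected.** Let s be the week of the first session, k the weeks between sessions, and R the week the week-12 questionnaire is returned. Even spacing is assumed, and the 24 weeks of access are taken to run from randomisation. The fifth session falls at week s + 4k. A patient is counted as a completer but was not one at the score when

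R < s + 4k ≤ 24, that is, (R − s)/4 < k ≤ (24 − s)/4.

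With the first session in week 1 (s = 1) and return at week 12 (R = 12), the limits are 11/4 = 2.75 and 23/4 = 5.75 weeks between sessions:

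| Weeks between sessions | Week of fifth session (1 + 4k) | Sessions done by week 12 | Status at week 12 under the undated rule |
|---|---|---|---|
| 1 | 5 | all 8 | correct |
| 2 | 9 | 6 | correct |
| 2.5 | 11 | 5 | correct |
| 3 | 13 | 4 | counted, though below 5 |
| 4 | 17 | 3 | counted, though below 5 |

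The limits move with the assumed start and return:

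- First session at week 0: above 3 and up to 6 weeks (R = 12), above 3.5 and up to 6 (R = 14), above 4 and up to 6 (R = 16).
- First session one interval after randomisation (s = k, so the fifth falls at 5k): above 12/5 = 2.4 and up to 24/5 = 4.8 weeks (R = 12), above 2.8 and up to 4.8 (R = 14), above 3.2 and up to 4.8 (R = 16).

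**Late starters.** With return at week 12, a weekly user is misclassified only if s + 4 > 12, so s > 8. A fortnightly user is misclassified only if s + 8 > 12, so s > 4. For example, a fortnightly user who starts in week 5 reaches the fifth session in week 13.

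The affected patients are therefore those who work at roughly three-week gaps or longer, or who start late, and who still reach five sessions within the access period. The article does not say how many there are.

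**The case against.** The strongest reply is that this is silence, not error. The rule fixes a threshold and does not say that sessions count at any time. A cut-off date is the kind of detail often left to a statistical analysis plan, and this is a condensed article. Part of that stands: a plan not shown here may contain a cut-off, and the article does not prove that the analysts would count late sessions. However, the article defines the completer set outright and applies that one definition to the main outcomes, which must include the primary outcome. Following the definition literally gives a worse week-12 set than a dated one would.

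The second reply is that the intended course puts the fifth session well before week 12. That also stands for patients who start promptly and work weekly or fortnightly. It does not cover the slower users whom the 12-to-24-week support period is designed to accommodate.

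The third reply is that the analysis is only supportive, and that any completers-only comparison is already selected on behaviour after randomisation. Both statements are true. Dating the count removes only the part of the selection that happens after the outcome.

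A reader might infer that the rule biases the per-protocol contrast by some number of WSAS points, or in favour of one type of support. The article does not support that. It gives neither the share of late completers in any arm nor how their scores differ from those of other completers. Secondary objective 4 poses a question about session numbers and does not report an imbalance.

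**Conclusion.** The point holds as a minor flaw in a stated definition. The completer rule is undated, the programme may be used to week 24, and the primary score is collected from week 12. The week-12 per-protocol set can therefore include patients who had fewer than five sessions when they were measured. The conclusion rests on reading the rule as written and on no unseen document adding a cut-off.

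The number of patients involved, and the size and direction of any bias, cannot be determined from the article. It should not be read as a challenge to the primary result: that analysis keeps patients in their randomised groups whatever treatment they received, and does not use the completer rule. The rule also suits the week-24 outcome much better, because the access period and that follow-up point roughly coincide.

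**What to change.** In the per-protocol sentence of Statistical analysis, tie the count to the outcome. For the week-12 analysis, completers are patients with at least five cCBT sessions logged up to the recorded receipt of the week-12 questionnaire. For the week-24 analysis, count sessions up to receipt of the week-24 questionnaire. The clause should be settled before the outcome data are analysed.

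No new data are needed, since session timing and time of receipt are already recorded. Receipt is only a proxy for the date the WSAS was filled in: a session done while the form is in the post would still count, and slower responders get slightly longer to reach five. It is, however, the date the article says is kept.

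The costs are two completer sets in place of one and a possibly smaller week-12 set. If a proportion p of completers is late and is lost equally from the compared groups, with the SD unchanged, the standard error is multiplied by 1/√(1 − p). For assumed values of 5%, 10% and 20% this gives 1.026, 1.054 and 1.118, a rise of about 3%, 5% and 12%. The revised set would still be non-randomised and should be reported as such.

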[25]. Also, weekly telephone tracking for cCBT for depression did not have an advantage over standalone cCBT
[26]. Finally, more frequent therapist contact via email (three times vs. once per week) did not improve outcomes and adherence with cCBT for panic
[27]. There is a need for further research to investigate whether keeping support sessions for cCBT for depression as brief as possible can save staff time without significantly compromising outcomes and acceptability, or whether offering longer support sessions can yield greater patient improvement or better completion rates.

Some cCBT studies
[21] use therapists who, whilst more expensive, may satisfy patients’ expectations and needs better than non-experts. Other studies use less experienced support staff, such as an administrator
[28,29], lay counsellors
[26] or psychology students
[22], who are easier to find and less costly to employ, but may be less effective or less acceptable, or may have hidden costs (for example, increased patient use of other services). Two studies
[28,29] directly compared cCBT with phone or email support from a therapist vs. an assistant and found similar symptom improvement in people with depression and generalized anxiety disorder (GAD) between the two groups. No studies have so far investigated the cost-effectiveness or explored patients’ experiences of receiving therapist vs. assistant support as an adjunct to cCBT.

This paper describes the protocol for a factorial RCT whose primary aim is to compare the clinical effectiveness, cost-effectiveness and acceptability of cCBT with two different types of support offered as an adjunct to it: brief vs. extended, and clinician vs. assistant support. To this end the study has the following primary objectives:

1. To compare clinical outcomes (depression and anxiety symptoms, functioning and quality of life) between brief and extended support for cCBT and between clinician and assistant support for cCBT.

2. To assess the cost-effectiveness of cCBT with brief vs. extended support and with clinician vs. assistant support and to estimate the cost for the National Health Service (NHS} of the population-wide implementation of the most cost-effective option.

3. To report and compare acceptability of cCBT (attrition, treatment usage and patient experiences) between brief vs. extended support and between clinician vs. assistant support.

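### The secondary between-group comparison of session-by-session electronic scores can turn a difference in log-in pace into a false symptom difference if it runs on session number; it should run on recorded time since randomisation.

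*Protocol article*

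**What the plan says.** The Statistical analysis section of the protocol article announces: "Secondary analysis will be carried out using the electronic data collected by the cCBT system in every session". It then adds: "The series of session electronic outcomes will be summarised and compared between treatment groups using repeated measures analysis". No time axis is named for this comparison.

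Other sections describe how the scores arise:

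- Data collection, on when a score exists: "Electronic data are collected automatically by the cCBT system during each cCBT session".
- Data collection, on timing: "The timing of electronic data collection is recorded by the cCBT system but it varies according to the frequency with which patients log into it".
- The cCBT section, on pace: "Patients go through BtB at their own pace, but it is suggested that they cover a module per week". Completing the programme within 12 weeks is an aim, not a rule.
- Ethical issues, on the window for log-ins: "Patients retain cCBT access for 24 weeks even if they choose not to speak to the support staff".
- Background: primary objective 3 makes attrition and usage outcomes to be compared between the randomised levels. The text before the objectives asks whether longer support might give better completion.
- Clinical outcomes: PHQ-9 and GAD-7 are also collected by post at weeks 12 and 24.

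For the postal questionnaires, the Statistical analysis section says that time of receipt may be used as a covariate. It says nothing similar for the electronic series.

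**The concern.** A comparison between randomised groups is protected when patients are measured at times, and in sets, that do not depend on what happens after allocation. Here both depend on log-in behaviour after randomisation.

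Two mechanisms need to be kept apart:

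- **Timing.** If one arm works through the programme faster, its session 8 falls earlier in recovery. Compared session by session, the faster arm then looks worse even when both arms improve identically over time.
- **Existence.** A patient who stops logging in has no later scores, and one who never logs in has none at all. If stopping relates to symptoms and does so differently by arm, the patients still observed are no longer comparable.

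At stake is a secondary claim that one type of support reduces symptoms more, when only pace or persistence has changed.

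**Working it through.** The protocol gives no figure for pace or session dropout by arm, so there is nothing to reproduce. The sizes below rest on assumed inputs.

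**Timing, by hand.** Eight sessions have 7 intervals. Assume that PHQ-9 falls by *s* points per week in both arms and that mean gaps between sessions are 1.0 and 1.5 weeks. The Telephone support section expects calls weekly or fortnightly according to the patient's speed, so gaps between 1 and 2 weeks are plausible. That arms differ in gap is purely an assumption.

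False difference at session 8 = 7 × (difference in gap) × *s*

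- *s* = 0.4: 7 × 0.5 × 0.4 = 1.4 points
- *s* = 0.2: 7 × 0.5 × 0.2 = 0.7 points
- *s* = 0.6: 7 × 0.5 × 0.6 = 2.1 points
- gaps 1.0 v 2.0 weeks, *s* = 0.4: 7 × 1.0 × 0.4 = 2.8 points

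In each case the true difference at equal time since randomisation is zero.

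**Timing and stopping, by simulation.** There were 300 trials per scenario, with 100 patients per factor level (200 randomised, two levels of each factor). Each patient had up to 8 sessions within 24 weeks, the first at time zero. Both levels had the same trajectory over calendar time. Assumed inputs were: baseline mean 14, between-patient SD 4.5, slope −0.4 per week (SD 0.25), residual SD 2.5, and 5% stopping per session unless shown otherwise (8% baseline rate in the last two rows). The analysis was generalised least squares with random intercept and slope covariance and sandwich standard errors. It tested the group-by-time slope at 5%. Differences are second level minus first.

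| Scenario | Session number: difference at session 8; rejection | Weeks since randomisation: difference at week 12; rejection |
|---|---|---|
| Equal pace | 0.05; 5.7% | 0.06; 5.7% |
| Gaps 1.0 v 1.5 weeks | −1.36; 66% | 0.05; 6.0% |
| Gaps 1.0 v 2.0 weeks | −2.85; 100% | −0.09; 5.3% |
| Equal pace, random stopping 5% v 12% per session | −0.04; 6.7% | −0.05; 6.3% |
| Equal pace, stopping driven by observed score, opposite directions by level | −0.01; 5.0% | 0.01; 6.0% |
| Equal pace, stopping driven by unobserved state, opposite directions by level | −0.46; 11.3% | −0.52; 10.7% |

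With 300 trials, the Monte Carlo standard error of a 5% rate is √(0.05 × 0.95 / 300) = 1.3 percentage points. Rates of 5 to 7% are therefore compatible with the nominal level.

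A further run used 70 patients per group, equal pace, and symptom-related stopping in one arm only, with about 45 to 47% of that arm reaching session 8:

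- Stopping on the observed score: raw difference in session-8 means −2.3; likelihood-type estimate 0.05.
- Stopping on the latent score: raw difference −2.1; likelihood-type estimate −0.3.

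The recorded dates therefore remove the timing bias under these assumptions. A likelihood-based model removes the stopping bias when observed scores explain stopping, and leaves about 0.3 to 0.5 points when they do not.

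**The case against.** The strongest reply is that the article never says session number is the time variable. Repeated measures analysis can run on actual time, log-in timing is recorded, and an article may leave such detail to an analysis plan that is not shown. It stands that actual time is not excluded. But the article does commit to comparing the series of session outcomes between groups, and session order is its natural reading. The point concerns that stated comparison and offers a better one from data already collected.

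Second, the protocol does not predict that usage will differ by arm. It asks whether it does, and its Background also cites studies in which more contact did not improve adherence. All arms get the same suggested pace and the same maximum number of calls. This stands: the bias is conditional on arm-dependent pace or stopping.

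Third, a reader might infer from the raw session-8 differences of about 2 points that selective stopping alone would seriously distort the planned analysis. The documents do not support that. The plan names a repeated measures analysis, not a comparison of session-8 means among those who remain, and under a likelihood-based version most of that difference disappears.

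Fourth, the analysis is secondary, and postal scores exist only for some of the electronic measures. Both are true, and both limit the scope of the point and its remedy.

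**Conclusion.** The point holds in a conditional form. If the electronic series is compared by session number and pace differs between arms, a false symptom difference follows. It is about 1.4 PHQ-9 points at session 8 for gaps of 1.0 v 1.5 weeks and a fall of 0.4 points per week, or 0.7 to 2.1 points for falls of 0.2 to 0.6. All of these inputs are assumed. Selective stopping is the lesser problem under a likelihood-based model: close to nothing when observed scores explain it, and about 0.3 to 0.5 points in the simulations when it depends on the unobserved state.

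A reader might go further and conclude that the trial's main result is at risk. It is not: the primary comparison uses the postal WSAS at week 12 in the groups as randomised and does not depend on log-ins. The change is worth making because the electronic comparison is planned between treatment groups and the repair is cheap.

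**What to change.** For the electronic symptom scores:

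1. Make the between-group comparison a likelihood-based mixed model with recorded time since randomisation as the time axis, analysing patients in their randomised groups.
2. For PHQ-9 and GAD-7, include the postal week-12 and week-24 scores in the same model, so that patients who stop or never start logging in still contribute if they return the questionnaires. No postal counterpart is described for the single-item and individual-problem scores, so this step does not apply to them.
3. Add a sensitivity analysis for stopping that depends on the unobserved state.
4. Present curves by session number descriptively, beside the number of sessions completed by arm, and draw no randomised comparison from them. Ratings of a single session's usefulness, relevance and ease belong here, since session number is their natural index.

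The cost is slightly more modelling, including a choice of shape for change over time, and reliance on missing at random given the observed scores. Joining postal and electronic scores also assumes that the two modes of collection give comparable values. No new data are needed: log-in timing is already recorded and the postal scores are already collected.
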